## Data management and quality assurance

All the quantitative tools will be piloted before the data collections start to ensure that the questions and the translations are comprehendible and that the type of responses obtained are as anticipated.

Names, telephone numbers and addresses will be recorded in order to keep track of the girls, but will be kept separate from other data and will only be available to particular staff. Each participant will be given a unique numeric identifier, and this number will be used when storing forms and recordings of interviews. The file linking the unique identifier with the name will be password protected and stored on a password protected computer. Only the data manager, the Principal Investigator and the local PI will have access to the linking file.

Pictures of the participants are personal information and they will just used for the purpose of ensuring that the correct participants are interviewed by limiting access to the pictures to a few project staff. The pictures of the participants will be taken with the password-protected tablets and named, and they will transferred to the project's password protected hard drive (which is locked in a safe in the project's Lusaka office) at the end of the interview round. When the pictures have been transferred to the hard drive, they will be deleted from the tablet. We will check that the dates of the pictures match with the dates when the interviews were conducted. We would like to store the pictures until the end of 2020 so we can confirm that it is the same person that is interviewed in each of the last rounds. At the end of the trial in December 2020, all the pictures will be deleted.

All collected consent and data forms will be stored in a locked cabinet or on password protected computers or tablets in a locked office. The offices (one in each district and one in Lusaka) where forms and computers are stored will only be available to senior study staff and will be locked whenever the staff leave. There will be 24 hour security measures to prevent that anyone breaks in to the office. When the trial is completed, all personally identifiable information will be deleted.

To ensure that data collectors are familiarized with the tablets and the software, data collectors will undergo thorough training in the use of the data collection software, and the interviews will be piloted. The forms will have check- and skip-rules inbuilt to minimize data entry errors. Checks for outliers and inconsistencies will be automatically conducted during data entry. Manual checks for outliers and missing entries will also be done by the data manager after the daily uploading of electronic data from the tablets to the database via internet. The plan was initially to store the data on a server owned by the University of Zambia, but since we think the data security will be better if we save the date on a secure server owned by the University of Bergen, we have obtained approval from the University of Zambia Bioethical Research Ethics Committee (UNZABREC) to save the data on a University of Bergen server instead.

In the qualitative process evaluation, we will seek permission to audio record the individual interviews and focus group discussions using digital recorders. Systematic note taking will be employed (field notes) in connection with observations and during the interviews where audio recording will not take place. The data from the individual interviews and focus group discussions will be transcribed and translated by professional transcribers. A senior researcher will on a daily basis review the transcripts to ensure that they contain word by word transcriptions and translations to English that retain original meanings with a particular caution to retain culturally embedded content.

Electronic data without personal identifiable information (entered quantitative data or digital recordings) will be stored in at least two locations at all times to ensure that there is always a back-up available. Further details of the data management procedures can be found in the Manual of operations.

## Statistical methods

The outcomes will be captured in binary, continuous or a time-to-event variables. Continuous variables that are right skewed will be log-transformed to obtained more symmetrical distributions. We will correspondingly employ Poisson regression or General linear models (GLM) of the binomial family with a log link (estimating risk ratios or RRs) and identity link (estimating absolute risk reduction), linear regression (estimating average effect or mean increase or decrease) or survival analysis using Cox regression. Each method will take account of the design effect of the clustering.

The data will be analysed with Stata (Stata Corporation, TX, USA) statistical software. We will compare outcomes between the three arms: the economic arm vs. the control arm, the combined arm vs the control arm, and the economic arm vs the combined intervention arm. Analyses will be by intention-to-treat (ITT), that is all participants, irrespective of whether they actually agree to the intervention allocated to them, will be included in the analysis according to the intervention arm the cluster they live in was allocated to. The Intracluster correlation (ICC) will be reported for all primary and secondary outcomes.

The primary outcomes will be measured in the final survey in February 2020 based on the participants’ responses to the questions “Have you ever given birth?” and “If yes, on which date and which year did you give birth?”. Reported childbearing before July 2019 will be recorded as “birth 8 months after end of the intervention period”. Girls who report a date of childbearing preceding their 18^th^ birthday, will be recorded as having “birth before 18^th^ birthday”. Girls who are married at the start of the intervention, will be excluded from the analysis of proportion of girls ever married/cohabiting before their 16^th^ or 18th birthday.

Descriptive statistics, such as means or medians and standard deviation or interquartile range will be used to describe continuous variables (the choice depending on the distributions). For categorical variables, frequencies and percentages will be calculated.

Proportions will be compared on both absolute and relative scales. Thus, relative risk, RR (and its analogue effectiveness, 1-RR) and absolute risk reduction (and its reciprocal “Numbers needed to prevent”) and their 95% CIs will be estimated using generalized linear models (GLM) of the binomial family with a log link and identity link, respectively. We will also employ logistic regression to arrive at ORs for the binary outcomes. Cox regression analyses will be used for estimating the effect of our interventions on time to first pregnancy. We will in all the analyses account for the cluster effect using robust standard errors. Random effects models will be used to assess population effects whereas fixed effects models will be used to assess individual effects. We will check whether the model fit is good by comparing the estimates from the GLM models with estimates obtained using Generalised Estimating Equations (GEE).

Where necessary we will deal with multiple absorbing events (for competing risks) and left censoring. For all these models, either Population-averaged or marginal versus subject-specific or conditional survival probabilites will be estimated.

Equity effects will be examined by comparing differential effects on the primary outcomes between wealth tertiles and educational tertiles.

Although this is a large randomized trial and randomization will be constrained to achieve balance with respect to predictors of outcome, any remaining imbalances of predictors of the outcomes in question will be adjusted for in the regression models. In order to evaluate potential confounding, we will stratify the analyses on baseline characteristics that are or can be dichotomized, and if the stratified analyses give indications of confounding rather than effect measure modification, we will adjust the analyses for these baseline characteristic if their inclusion in the statistical model changes the effect estimate with more than 5% or substantially increases its statistical precision. For continuous variables such as age, we will also explore whether there is effect measure modification using appropriate interaction terms and, if not, adjust for variables using the criteria described above. For analysis where adjustment for several baseline characteristics turn out to be necessary, e.g. in (predefined) sub-group analyses, we will use statistical modelling approaches, such as those using the Akaike information criterion to arrive at a final model.

Interaction analysis will primarily be conducted on an additive scale, according to Rothman (Kenneth R. Rothman-Epidemiology, an introduction) and Anderson *et al*. (European Journal of Epidemiology (2005) 20: 575-579)

Instrumental variable analyses will be used in an attempt to estimate the causal effects of exposure to each intervention component (X) on the outcome (Y). (The random allocation (Z) will be the instrument.)

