| **Parameter** | **Assumed level** | **Comment** |
| --- | --- | --- |
| Incidence of births before girls’ 18th birthday | 0.08 | We assume that 27% of girls in the control arm will have given birth before their 18th birthday. This corresponds to an average incidence rate of (27%-3%)=8% per year over the average 3 year period (from the time the average age is 15). |
| Effectiveness (i.e. (1-RR)×100 of economic intervention vs control | -25% | I.e. the incidence in economic intervention arm assumed to be 0.06 |
| Effectiveness of combined intervention vs control | -40% | i.e. the incidence in combined intervention arm assumed to be 0.048 |
| Effectiveness of combined intervention vs economic intervention | -20% | The combined intervention will offer [1-(0.0.048/0.06)], i.e. 20% more relative protection than the economic intervention alone. |
| Cluster size | 28 | Average number of girls in grade 7 in the selected schools is 31. If we assume that up to 10% may be lost to follow up by the time of measuring the outcome, the average cluster size will be 28 |
| Person years per cluster | 84 | If 28 participants are followed up for 3 years on average, person years per cluster are 84. |
| Coefficient of variation (k) | 0.15 | The ICC was 0.00737 for “ever pregnant” after intervention period in cash transfer trial in Malawi (estimate obtained from [name]). This corresponds to k=0.15 when the total proportion who have given birth by this time is 0.27 [51]. |
| Z_1_ (acceptable alpha error level) | 1.96 |  |
| Power for comparison of economic intervention vs combined intervention | 70% | We need 63 clusters in each of the intervention arms to have 70% power to detect the assumed difference |
| Power for comparison of economic intervention vs control | 80% | We need 39 clusters in each arm to have 80% power to detect the assumed difference. The PASS power calculator for incidence rates does not allow for unequal trial arms, but the PASS function for proportions indicates that 63 economic and 31 control will give slightly higher power^[[5]](#endnote-2)^ |
| Power for comparison of combined intervention vs control | >95% | We need 23 clusters in each arm to have 95% power to detect the assumed difference. |
|  |  |  |

*Assumptions for sample size required to measure the primary outcome ‘proportion of girls who sit for grade 9 exam’*

| **Parameter** | **Assumed level** | **Comment** |
| --- | --- | --- |

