| **Follow-up contacts** | All the girls in the intervention and control arms will be contacted every 6 months to update contact information and ask questions about school attendance, employment, marital status and childbearing, health care seeking, and whether they have received the cash transfers and/or participated in the youth club meetings. To monitor adverse events that can be attributed to the trial, girls will also be asked whether they have experienced problems due to their participation in the trial. In the fourth follow-up interview (taking place during the first two quarters of 2018) additional questions will be asked about communication about sexual and reproductive health issues.  In order to make it easier for the participants to respond to the more sensitive questions, Audio Computer Assisted Self-Interviewing (ACASI) will be used for questions 69-82. This will be done by giving the participants headsets so they can listen to the questions being read to them and they will be given privacy to fill in the correct responses on the tablets themselves. ACASI-technology has been shown to increase participants’ perceptions of privacy and anonymity and it appears to reduce social desirability bias [52, 53]. In addition, the item count technique [54, 55] will be used. This is an indirect questioning technique where the participants indicate how many of a set of statements are true for them, rather than whether each of the individual statements are true or false. If the girl cannot be found at school or at home at the time of the follow-up interview, call centre research assistants will attempt to reach her by phone.  In the third follow-up round we experienced challenges in several of the control schools with finding the participants because many of them were not in school any more. In order to motivate the participants to come to the school to be interviewed, we will increase the transport allowance provided for control participants from K20 to K50 per interview in 2018 and further to K75 in 2019 and K100 for the final interview in 2020. For the participants in the intervention arms, we do not think it is necessary to provide such an allowance during the period when they are receiving economic support, and thus a transport allowance of K75 / K100 will only be provided for interviews in 2019 and 2020. The participants will then have finished grade 9 and we expect a large proportion of them to move away from the study areas, either to go to grade 10 in a secondary school or to get married or work. This implies that they will either have to travel to come back for interviews and need to be compensated for the costs and time that this requires. And for those that move far away, they will have to keep their phone number active for us to be able to interview them over the phone and many of them will also have to call us to inform us when they will be available, and thus the compensation should be sufficient to cover the costs of this.  Around the time of the fourth follow-up interviews with the RISE participants in the first half of 2018, their parents/guardians will also be invited to come to parent meetings where they will be asked take part in an interview. Parents/guardians who do not come to the meeting will be sought at home. The questions in the parent interview pertain to expenses they have had in the previous 6-12 months related to food, education, health care and other expenditures, and about their attitudes to early marriage, early childbearing, contraceptive use and education. A travel allowance of K50 will be offered to the guardians who are interviewed.  The research assistants will be asked to take selfies of themselves with the participants to document that they have interviewed the correct participants. The trial participants in most cases live far away from each other and the research assistants who do the interviews travel alone (or with a driver) on a motorbike to find the participants. Thus, even if there is a supervisor who makes unannounced monitoring visits to observe the research assistants twice per month, most of the interviews are done without other project staff being able to observe them. We are worried that some of the research assistants may be tempted to manufacture some of the interviews, particularly when it is difficult to find participants because they have moved (which is the case for an increasing proportion of our participants). We expect that such pictures will make fabrication of interviews less likely. |

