| **Case report form** | We will keep an electronic Case report form (CRF) for each participant where we will record information from the eligibility screening, contact information, consent issues, social problems experienced due to the trial, cash transfer issues, reasons for loss to follow-up etc. Information about the attendance in youth club meetings in the community component will be recorded on paper forms and will be entered into the electronic case report form for each participant in the combined intervention arm. Information about cash transfers and payment of school fees will also be recorded electronically and this information will automatically be updated in the electronic case report form. |

It seems that participants who are lost to follow-up are particularly likely to be married, and since we know that marriage is closely associated with early childbearing, we are concerned that loss to follow-up may introduce bias in the measurements of the outcomes related to childbearing and marriage. Thus we are requesting permission to record information about marital status and childbearing of participants who have been lost to follow-up. This information will be used in a secondary analysis of the proportion who has given birth and who are married.

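### The primary birth outcomes are taken from the final survey alone, so a birth reported at an earlier six-monthly contact does not count if the girl misses that survey

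*Protocol*

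**What the plan says.** - **Source of the outcomes.** Statistical methods states: "The primary outcomes will be measured in the final survey", which it dates to February 2020, from the girl's own answers to two questions. The first question is whether the girl has ever given birth; the second is "If yes, on which date and which year did you give birth". No other source is named.
- **Coding.** The reported dates code both birth outcomes. For the 8-month outcome: "Reported childbearing before July 2019 will be recorded as" an event. For the other: "Girls who report a date of childbearing preceding their 18^th^ birthday, will be recorded as having" the before-18 outcome.
- **Other data on births.** Under Follow-up contacts, Table 1 has girls in all arms contacted every six months to "ask questions about school attendance, employment, marital status and childbearing".
- **Who is lost.** The paragraph after Table 1 reads: "It seems that participants who are lost to follow-up are particularly likely to be married". It adds that marriage goes with early childbearing and that loss may therefore bias the childbearing outcomes. Information on lost girls goes to a secondary analysis there. The list of protocol changes describes it as reports from teachers, neighbours and family, for sensitivity analyses.
- **Scale.** The change list records that the birth measures became incidence rates in July 2016. The Sample size section plans on person-years: "If 28 participants are followed up for 3 years on average, person years per cluster are 84".

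**The concern.** A girl's own report of a birth, made to trial staff before she was lost, is primary-quality information. The stated rule gives it no place, so she contributes neither an event nor time at risk.

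The clearest case is the 8-month outcome. Both timelines show a contact round in September to December 2019, after the July 2019 cut-off. A girl interviewed then has that outcome fully observed, yet it is missing if she is not found in 2020.

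The rule also fits poorly with two other commitments. Intention-to-treat is described as including all participants, and the outcomes are rates, for which contacts before loss would supply person-time.

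Three things are at stake:
- Absolute birth risk is understated if lost girls give birth more often.
- The relative comparison is biased if loss, or its link to births, differs by arm.
- Power falls with the lost person-time.

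Differential loss is plausible. Table 1 reports trouble finding participants in several control schools, and the incentive to respond differs by arm while economic support is being paid.

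**Working it through.** **1. The plan's own figure.** For birth before 18, economic against control, the inputs from the Sample size section are rates of 0.08 and 0.06, 84 person-years per cluster, k = 0.15, z = 1.96 and 80% power. The usual cluster-trial formula for rates is

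c = 1 + (1.96 + z_power)² × [(λ0 + λ1)/y + k²(λ0² + λ1²)] / (λ0 − λ1)²

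= 1 + 7.849 × [0.14/84 + 0.0225 × 0.0100] / 0.0004 = 38.1, that is 39 clusters per arm, as stated. The same formula gives 36 for the 8-month outcome (stated 36). The design therefore rests on person-time, and its sample size is not in dispute.

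**2. Effect of loss on risk and risk ratio.** Let L be the proportion lost in an arm and r the birth risk of lost girls relative to retained girls. The risk seen among retained girls is

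observed risk = true risk / (1 − L + L × r).

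The true risks are 27% in control (Sample size) and 0.75 × 27% = 20.25% in the economic arm. The protocol allows for 10% loss. It gives no r; 1.5 to 2.5 is an assumption. The unequal split of 7.5% and 12.5% is also assumed; it averages 10% and differs by 5 points.

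| r | Control risk seen, 10% loss in both arms | RR, 10% loss in both arms | RR, economic 12.5% and control 7.5% lost | RR, economic 7.5% and control 12.5% lost |
|---|---|---|---|---|
| 1.5 | 27/1.05 = 25.7% | 0.75 | 0.75 × 1.0375/1.0625 = 0.73 | 0.75 × 1.0625/1.0375 = 0.77 |
| 2.0 | 27/1.10 = 24.5% | 0.75 | 0.75 × 1.0750/1.1250 = 0.72 | 0.75 × 1.1250/1.0750 = 0.78 |
| 2.5 | 27/1.15 = 23.5% | 0.75 | 0.75 × 1.1125/1.1875 = 0.70 | 0.75 × 1.1875/1.1125 = 0.80 |

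With equal loss the ratio holds, but the risk difference, which the protocol also reports, shrinks from 6.75 points to 6.75/1.05 = 6.4 or 6.75/1.15 = 5.9.

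**3. Share of births missed.** This is L × r / (1 − L + L × r). At 10% loss it is 0.15/1.05 = 14%, 0.20/1.10 = 18% and 0.25/1.15 = 22% for r = 1.5, 2 and 2.5.

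**4. Power.** With the same variance, 31 control and 63 economic clusters of 31 girls, and all time of lost girls dropped, power for economic against control is 84.5% with no loss, 81.1% at 10% loss and 77.0% at 20%. The plan already budgets for the 10%.

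**5. What these figures do not show.** They give the whole effect of losing girls from the final survey. Using the earlier reports recovers births and time up to the last contact. Births after it stay unobserved. The documents do not allow the recoverable part to be computed.

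**The case against.** A reader might infer that the outcomes rest on a bare yes/no answer and that the six-monthly reports are thrown away. The text does not support either. The date of birth is asked and used, so respondents have event times, and Poisson and Cox models are both allowed. Nothing says the interim reports are unused; they simply have no stated role. A statistical analysis plan, not seen here, may deal with missing outcomes and censoring.

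The key sentence also looks unreconciled. It dates the final survey to February 2020, against the last quarter of 2020 in Table 1 and mid to late 2020 in the timelines. It speaks of the primary outcomes in general, though its two questions cannot measure sitting the grade 9 exam. It may not have been meant as an exclusive rule.

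The protocol partly covers the problem through tracing, retention payments and third-party reports on lost girls. Nor is a 5-point gap in attrition simply accepted: under Data monitoring, that gap, or follow-up below 90%, obliges the investigators to submit a corrective plan.

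Using interim reports has its own cost. Masking efforts are promised for the final-survey team. Interim contacts ask about cash and club attendance, which can reveal the arm. During the intervention, non-response stops the economic support, while controls receive only an allowance, so ascertainment could differ by arm.

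Much of this stands and limits the claim. It does not remove the core: the protocol does fix a source, and a girl's own earlier report falls outside both that source and the analyses described for lost girls.

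**Conclusion.** The point holds as a defect in the stated outcome definition. The final survey is the only named source for the primary birth outcomes, although six-monthly self-reports are collected and the protocol recognises that loss may bias these outcomes.

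The size is conditional. With r between 1.5 and 2.5 and 10% loss in every arm, the control risk reads 25.7% to 23.5% instead of 27%, with no bias in the risk ratio. With 7.5% against 12.5% loss, a true 0.75 reads 0.70 to 0.73 if the economic arm loses more, or 0.77 to 0.80 if control loses more.

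A reader might infer that the trial's risk ratios are bound to be biased, or that the lost girls are known to be those at highest risk. Neither follows. Equal loss with equal r leaves the ratio intact, and the link to marriage is the protocol's impression, given without a figure.

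**What to change.** In Statistical methods, define the event for each birth outcome as a first birth after randomisation that the girl herself reports at any six-monthly contact or at the final survey. Count person-time from randomisation to the earliest of that birth, the 18th birthday (or the July 2019 cut-off for the 8-month outcome) and the last completed contact. Analyse by Poisson regression, which the section already allows, with a log person-time offset and cluster-robust standard errors.

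Also state:
- a rule for birth dates that conflict between rounds;
- a rule for girls who had already given birth at baseline, who are eligible (the sample size subtracts 3%, apparently for them); for example, not at risk for a first birth;
- that the final-survey-only analysis and the third-party reports are kept as sensitivity analyses;
- one date for the final survey, reconciled across Statistical methods, Table 1 and the timelines.

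The cost is protocol wording and some programming; no new data are needed. The downside is that interim reports are less well masked and response incentives differ by arm. The final-survey-only analysis would show whether that matters. Third-party reports remain necessary because births after the last contact are still unobserved.
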